### 2.2. Sample Size

Based on the previous study [40], the rate of irrational use of drugs by guardians for their children is 40% to 70%. Through our educational intervention, we hypothesized a 15% reduction in the rate of irrational drug use among children. We set α = 0.05, 1 − β = 0.9. We used software, Sample Size 2.0, to calculate the sample size, and 231 participants are required for the intervention and control groups. Taking into account the lost population, the invalid questionnaires, and the low response rate, we increased the sample size by 55%, to a total sample size of 720. We will select 180 school-aged students in every school. For each child included in our study, we will also invite their caregiver to participate in the study. In four primary schools, we chose 720 students and 720 caregivers. The sampling process is shown in Figure 1. We also invited teachers to help us to do our study. They are the bridge of communication between researchers and caregivers. Caregivers may not follow the orders from researchers, however most parents will follow tasks that are assigned by the teacher and, therefore, we will invite teachers to help us to implement a smooth intervention. In addition, they will help the researchers to distribute and collect the questionnaires from the children and caregivers. Before the intervention, we will give training to the teachers so that they will know more about our study and will clearly know their duty. In each class, we will invite 1 head teacher to cooperate with us.

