## 2. Materials and Methods

### 2.1. Study Design

We will conduct a multistage cluster randomized controlled trial at the school-level. Our study will be carried out in primary schools in the Shaanxi Province, western China. According to the economic level of the Shaanxi Province, two clusters were formed: developed areas, where we chose Baoji, and Weinan from the less developed areas. The chosen primary schools from both of the study sites met the following inclusion criteria: (1) Schools must be willing to take part in our study; (2) Schools should be in urban areas with enough teachers and students. In rural areas, most young people need to go out to work and earn a living, leaving the elderly to look after the children. Socio-demographic characteristics are quite different between rural and urban areas, so we only include urban primary schools. (3) Schools are theoretically matched and are comparable with each other in terms of school size and teaching level; (4) Must be public primary schools because private primary schools are mainly composed of students with higher family incomes. (5) Two schools in each city must be in different districts or in different streets. The distance between the two schools in each city must be more than 5 km. Based on the inclusion criteria and the referenced CONSORT (Consolidated Standards of Reporting Trials) statement for randomized trials [39], a final selection of two primary schools in each city will be made. In total, there are 804 public primary schools in Baoji and 638 public primary schools in Weinan. Among these schools, in Baoji there are 37 schools in urban areas and 767 in county or in rural areas. For the schools in urban areas, 10 schools are unwilling to participate in our study and 17 schools are small scale (which have less than three classes in the fifth grade or less than 1500 students in schools). Taking the distance between the two schools in the same city into account, we chose two schools from the remaining 10 schools. In Weinan, there are 23 schools in urban areas and 615 in counties or in rural areas. The sampling process was similar in Weinan and we have depicted it in Figure 1 (The sampling process). In each city, one primary school will be randomly selected for the intervention group and the other will serve as the control group. The study participants will be chosen from the class level and in every school we will select three to five classes from the fifth grade at random. Participants will be selected based on the inclusion criteria from the chosen classes and they will be blinded on their assigned group.

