This study is with some deficiencies. The sample size is not large enough due to the heavy learning pressure, fewer primary schools in only one province are included, and rural primary schools are not included in our study, therefore generalization cannot be made. However, after this research, we hope to extend the intervention to more students and caregivers through the Ministry of Education. In addition, we cannot make sure that all of the participants will read the educational materials and will take part in the training sessions, which may have an effect on the final results. However, we will attempt to minimize this effect. Before the training session, each participant will receive a message reminding them to attend it on time and will be required to sign in. What is more, the content of the training session and the educational materials will be repeated. Lastly, the intervention period will only last for 3 months because of limited funding and time, and so further study will need to be conducted to observe the impact of long-term interventions.

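### The 231 per group is an individual-randomisation number, so the stated 90% power is not delivered by a trial that randomises four schools

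*Protocol article*

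**What the plan says.** Section 2.1 (Study Design) makes the school the unit of randomisation: "We will conduct a multistage cluster randomized controlled trial at the school-level". Allocation is within city: "In each city, one primary school will be randomly selected for the intervention group and the other will serve as the control group". With two cities, that is four schools, two per arm.

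Section 2.2 (Sample Size) cites an earlier study for the baseline and states that "the rate of irrational use of drugs by guardians for their children is 40% to 70" (per cent). It adds that "we hypothesized a 15% reduction in the rate of irrational drug use among children" and sets the error rates: "We set α = 0.05, 1 − β = 0.9". From these it reports the result: "We used software, Sample Size 2.0, to calculate the sample size, and 231 participants are required for the intervention and control groups". It then adds 55% for loss to follow-up, invalid questionnaires and low response, and arrives at 720 in total, 180 per school. No ICC, design effect or number of clusters enters the calculation.

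Section 2.5 (Outcome Indicators) confirms that the powered quantity is the caregivers' primary outcome, a proportion.

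**The concern.** Caregivers whose children attend one school may resemble each other more than caregivers from different schools. Whole schools are allocated, so the effective sample size is smaller than the head count, and the between-school variance must be estimated from four schools. A sample size for independent people ignores both facts.

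If the 90% figure stands, a non-significant result from a school-level analysis could be read as good evidence against a 15-point effect, when the design had little chance of detecting one. Readers planning similar trials would also inherit a calculation that does not fit its design; the Introduction offers this protocol as a model.

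**Working it through.** **Inputs.** From section 2.2: baseline 40% to 70%, reduction 15%, alpha 0.05, power 0.9, 231 participants, uplift 55%, 180 per school. From section 2.1: two schools per arm. Inferred, because the article does not state them: baseline 55% (the midpoint), an absolute 15-point reduction, a two-sided test. Assumed: ICC of 0.001, 0.005, 0.01, 0.02 and 0.05.

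**Step 1: reproduce 231.** Pooled formula for two independent proportions, p1 = 0.55, p2 = 0.40, mean 0.475:

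n = [1.960 × √(2 × 0.475 × 0.525) + 1.2816 × √(0.55 × 0.45 + 0.40 × 0.60)]² / 0.15² = [1.960 × √0.49875 + 1.2816 × √0.4875]² / 0.0225 = 230.83, so 231 per arm.

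60% versus 45% gives the same number. A relative 15% reduction needs at least 353 per group anywhere in the 40% to 70% range, so it does not reproduce 231. Since 231 × 2 × 1.55 = 716, close to 720 = 4 × 180, the 231 is per arm. The match is exact at a design effect of 1, so no clustering allowance is hidden in it.

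**Step 2: can the uplift serve as a design effect?** If the losses occur as planned, about 231 per arm remain (115.5 per school) and nothing is left for clustering. If there is no loss at all, 360/231 = 1.56 is available. Solving 1 + 179 × ICC = 1.56 gives ICC ≈ 0.003. Only at or below that value does the normal approximation keep 90%.

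**Step 3: effect of the ICC, normal approximation.** Design effect DE = 1 + (m − 1) × ICC. Standard error = √[0.4875 × DE / (2m)]. Power = Φ(0.15/SE − 1.960).

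| ICC | DE, m = 115.5 | Power, 231 per arm | DE, m = 180 | Power, 360 per arm |
|---|---|---|---|---|
| 0.001 | 1.11 | 87% | 1.18 | 96% |
| 0.005 | 1.57 | 74% | 1.90 | 84% |
| 0.01 | 2.15 | 61% | 2.79 | 69% |
| 0.02 | 3.29 | 44% | 4.58 | 48% |
| 0.05 | 6.73 | 24% | 9.95 | 25% |

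Example: at ICC 0.01 and m = 115.5, SE = √(0.4875 × 2.145 / 231) = 0.0673, 0.15/0.0673 = 2.23, and power is 61%. Using the pooled variance for the test's critical value lowers these figures by at most about one percentage point.

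As m grows without limit, the effective number per arm tends to 2/ICC. Once ICC reaches 2/231 = 0.0087, no number of participants in two schools per arm gives 90%.

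**Step 4: effect of having only four schools, kept separate.** Set ICC = 0, so that the design effect plays no part, and compare four school means by a t-test on 4 − 2 = 2 degrees of freedom (noncentral t). Power is 44% with 231 per arm and 58% with 360 per arm. A comparison paired by city has 1 degree of freedom and gives 20% and 25%.

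**Step 5: both together.** On 2 degrees of freedom with 231 per arm, power is about 25%, 19% and 12% at ICC 0.01, 0.02 and 0.05.

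**The case against.** **The size of the loss in Step 3 depends on an ICC that the article does not give.** This stands. With full response, the normal approximation gives 96% at 0.001 and about 90% near 0.003, so a reader who believes in a very small ICC and no loss could call the design adequate by that method. It does not rescue the claim: it needs the whole uplift to go unused, and it ignores the degrees of freedom, which hold a school-level test to 58% at best even at ICC zero.

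**Matching and baseline data may recover precision.** Section 2.1 requires schools comparable in size and teaching level, and pre- and post-intervention data are compared between groups. Either could reduce residual between-school variance. The calculation uses neither, and a test paired by city leaves 1 degree of freedom. They qualify the size of the loss, not the error.

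**A full protocol or analysis plan may handle clustering.** It may, and silence on the analysis method is not the point. The article itself states a design, a calculation and a power that do not fit together. An analysis that respects clustering would expose the shortfall, not remove it.

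**Two stronger readings are not supported.** A reader might infer that the Discussion contradicts the 90% when it says "The sample size is not large enough due to the heavy learning pressure". That sentence goes on to the small number of schools, the single province and the missing rural schools, and concludes on generalisation. It is a caveat on external validity and does not retract the power. A reader might also infer that the Conclusions make wider roll-out depend on a significant result. They make it conditional on the measures showing effectiveness and state no significance rule.

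**Conclusion.** The point holds. The 231 per group is an individual-randomisation number, and the stated 90% power does not belong to a design with two schools per arm. That finding rests on the article's design and calculation, with the 55% versus 40% rates and the two-sided test inferred from the exact match; it does not rest on a particular ICC.

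The size has two parts. The missing design effect costs from a few percentage points to most of the power, depending on an ICC that has to be assumed. The number of schools caps a school-level test on 2 degrees of freedom at 44% or 58% whatever the ICC, and lower still if paired by city. Because this is the calculation for the caregivers' primary outcome, the statement needs correcting.

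**What to change.** In section 2.2:

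- Say that 231 per arm is the number for individual randomisation, and state the rates, the absolute scale of the reduction and the sidedness behind it.
- Add the design effect 1 + (m − 1) × ICC over a stated ICC range that includes values below 0.01, for both 115.5 and 180 per school.
- Replace the 90% with the power that two schools per arm give under a school-level analysis, naming the degrees of freedom.

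Report the effect with an interval computed at cluster level, and state that a null result will not be taken as evidence against a 15-point effect. Describing the trial as estimating effect size, ICC and feasibility is an option that follows from the restated power; it is not required.

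The change is rewording. It needs no extra participants or data, and its cost is a less favourable stated power. It corrects the claim but does not raise the power; under the normal approximation, more participants in the same four schools could not restore 90% once the ICC reaches about 0.009.

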### 2.3. Eligibility Criteria for Participants 

We will include healthy children (aged 8–12) and caregivers who have the primary responsibility for the children and have normal understanding, cognitive, and communication skills.Children and caregivers who volunteer to participate in this study must have lived in the sample area for more than a year and those with less mobility will be included. A written informed consent will be collected from all of the participants.We will exclude children with severe liver, kidney disease, chronic diseases, and severe syndromes.We will preclude caregivers who work in the health field.

### 2.4. Intervention Procedures

The purpose of the intervention is to change the knowledge, attitude, and behavior of guardians about the use of antibiotics for children with upper respiratory tract infections and, at the same time, to improve children’s knowledge about antibiotics use and to help them build awareness of preventing infection. We have created a WeChat (the most popular web-based social media tool in China) official account, through which we will push educational materials about the rational use of antibiotics to guardians. Only participants in the intervention group will have access to the information in the WeChat platform. Besides, participants are required to not share the information to others during the intervention period. For those caregivers who do not have WeChat accounts, we will distribute paper education materials separately, which will be the same as the electronic one. The educational materials are from the Center for Disease Control and Prevention in America [41]. Under the circumstance of China, we will translate the educational materials into Chinese and will make them easy to understand. We developed booklets about rational antibiotics use in children which cover the basic concept of antibiotics, antibiotic resistance, bacterial and viral infections, indications of antibiotics, and problems that can be encountered with the use of antibiotics and so on. The booklets will be taken home by the students. Both the students and the caregivers are required to study the booklet with commands from the teachers. Additionally, every month within a 3-month period, experts in the field will conduct a 1.5-h interactive training session for the children and their caregivers, and before each training session, we will issue them with the teaching materials. The content of the training session mainly includes four aspects: knowledge on microorganisms, the spread of infection, the prevention of infection, and the rational use of antibiotics for respiratory diseases. However, the training session for the caregivers will focus on the rational use of antibiotics and that for the children will concentrate on the knowledge of microorganisms, the spread of infection, and the prevention of infection. In the control group, both the children and caregivers will have no access to any intervention measures.

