
This study will be divided into three phases: pre-intervention, intervention, and post-intervention. In the pre-intervention phase, we will administer the KAP questionnaire and the Knowledge-Retention questionnaire to the caregivers and children to collect baseline data. Baseline data will be collected from June 2018. After baseline data is collected, we will implement health education interventions for the children and guardians, respectively, and it will last for three months. Immediately after the intervention, we will send questionnaires to the studied groups, that is, the children and caregivers. However, for school-aged children, we will again send the Knowledge-Retention questionnaire to them to evaluate the retention of knowledge one month after the intervention. Pre and post-intervention data will be compared between the intervention and the control groups, and we will then analyze the results to assess the impact of the interventions on antibiotics use among children.

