Children are the future users and prescribers of antibiotics, and so the rational use of antibiotics in children is not only significant to children, but also to their guardians. Both populations lack knowledge about antibiotics and, in addition, the easy accessibility of antibiotics without prescriptions is largely seen in China. Therefore, educating children and caregivers will be challenging but indispensable. During implementing the intervention study, we have difficulties to overcome. Firstly, because of the time-consuming nature of intervention studies, recruiting schools and participants is more difficult than for cross-sectional studies. Secondly, in theory, we hope that every participant in the intervention arm will complete all of the intervention measures, however, this is difficult to achieve. Besides, it is critical to control the contamination between the control group and the intervention group. Our study has some advantages. First, it is closely linked to the theme of antibiotic resistance, and we carry out an educational intervention about the rational use of antibiotics for children and caregivers from the school level to make up for the deficiencies in the domestic research in this area. Moreover, the content of our training sessions is not only limited to the rational use of antibiotics to treat infection, but it also focuses on how to prevent infection. Besides, we not only set a control group, we also compare the data before and after the intervention so that we can evaluate the net effect of the intervention. Last but not least, WeChat has become a way of life for the Chinese. People started to use it for text messaging, life moment sharing, and watching videos and so on. Data in 2016 showed that it attracted some 889 million monthly active users [48]. In our study, we will combine paper educational materials with network technology and we will implement interventions through the WeChat platform, therefore, the intervention measure in our research is novel. 

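### The no-sharing rule ends with the three-month intervention, but the children are tested again a month later, so the one-month comparison between arms is less protected against contamination than the immediate one

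*Protocol article*

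**What the plan says.** Section 2.4 of the protocol article puts a time limit on sharing: "participants are required to not share the information to others during the intervention period". Section 2.1 gives the length of that period: "we will implement health education interventions for the children and guardians, respectively, and it will last for three months".

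Section 2.1 then sets two assessments after the intervention. The first covers both populations: "Immediately after the intervention, we will send questionnaires to the studied groups, that is, the children and caregivers". The second is for the children only and is meant "to evaluate the retention of knowledge one month after the intervention".

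Two other safeguards in section 2.4 carry no end date: "Only participants in the intervention group will have access to the information in the WeChat platform", and "In the control group, both the children and caregivers will have no access to any intervention measures". Section 2.1 adds that allocation is by school and that the two schools in a city lie more than 5 km apart.

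On materials, section 2.4 says: "The booklets will be taken home by the students". No section describes their return. The Discussion states that "it is critical to control the contamination between the control group and the intervention group".

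**The concern.** The rule that stops intervention families from passing material on is worded to lapse when the intervention ends. The children's last questionnaire comes a month after that. During that month a family can forward content, or lend a booklet, without breaking any instruction given to it.

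The comparison between arms at one month is at stake. If some control children see the material, their scores rise and the difference shrinks. A reader would see a smaller difference at one month than immediately after the intervention and could take it for forgetting, when part of it was leakage. This could not be repaired once the data were in.

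Section 2.5 makes the percentage of correct answers to each question the children's primary outcome and names no time point. The one-month wave therefore cannot be set aside as secondary on the article's own terms.

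**Working it through.** The point is one of timing, and no figure stated in the plan depends on it. The sample size in section 2.2 concerns the caregivers' outcome.

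**Timeline**, counting from the start of the intervention:

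| Event | Month | Source | Covered by the no-sharing rule? |
|---|---|---|---|
| Intervention | 0 to 3 | 2.1 | Yes |
| First post-test, children and caregivers | 3 | 2.1 | Yes, in effect: it follows at once |
| Repeat test, children only | 4 | 2.1 | No |

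Uncovered interval: 4 − 3 = 1 month. It precedes only the children's repeat test.

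**Do the other safeguards fill the gap?** The WeChat limit says who may enter the account. The statement on controls says what the study will give them. Neither prevents a participant from passing content to someone else. The article has a separate rule for that, and it is the one with an end date.

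**Scope of the rule.** It follows directly on the sentences about WeChat content pushed to guardians. Whether it also covers booklets and session materials is unclear.

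**Direction and possible size.** Let D be the true difference between arms at month 4, and c the fraction of control children who gain the full intervention effect through leakage. The observed difference is then D × (1 − c). The documents give neither c nor D, so the values below are assumptions, with D = 20 percentage points correct for illustration:

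- c = 0.05: 20 × 0.95 = 19 points (95% kept)
- c = 0.10: 20 × 0.90 = 18 points (90% kept)
- c = 0.20: 20 × 0.80 = 16 points (80% kept)

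For a given c this is the most that leakage would plausibly take away. It supposes that a forwarded post or a borrowed booklet does as much as the whole programme, including the three expert sessions.

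**Effect on a retention reading.** If a fraction r of the immediate difference is truly kept at month 4, the ratio of the two between-arm differences reads r × (1 − c). With r = 0.9 and c = 0.10 (both assumed), that is 0.9 × 0.90 = 0.81, so leakage looks like extra forgetting. The change within the intervention arm from month 3 to month 4 contains no control data, so c does not enter it.

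I do not turn this into power for the children's outcome. That would need the item-level rates and the variation between schools, which the article does not give.

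**The case against.** The strongest reply is that the exposure is narrow. Whole schools are allocated, and the two in a city are in separate districts or streets and more than 5 km apart. The first post-test leaves essentially no uncovered interval, and every caregiver outcome is measured there. WeChat content goes to guardians and deals with antibiotic use. The listed booklet topics bear mainly on the microbe and antibiotic sections of the children's questionnaire, not on its three hygiene sections (2.4, 2.6). If both arms are retested, a rise among controls between the two tests would give a warning, though it could also be learning from repeated testing. All of this stands and keeps the point modest. It does not close the gap: distance does not stop forwarding on WeChat, which the Discussion describes as widely used for messaging and sharing.

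A second reply is that this is a condensed article and the participant instructions may say more. That would answer an omission. Here the article states an end date, and that date falls before the last assessment.

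A reader might go further and infer that the one-month test does not measure retention at all. The documents do not support that. Retention can still be read from the intervention arm's own change between the two tests. Nor does the article say that WeChat pushes continue after month 3, or define retention as recall without materials. The booklets were taken home and no return is described, which bears on how the one-month result should be labelled. It does not make the result invalid.

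**Conclusion.** The point holds in a limited form. The no-sharing rule stops one month before the children's last questionnaire, so the between-arm comparison at that wave is less protected against contamination than the immediate one. Any bias from leakage is towards no difference. Its size cannot be derived from the documents, and the range of 80% to 95% of the difference kept rests wholly on assumed leakage of 20% to 5%. School-level allocation and the distance between schools make heavy leakage less likely.

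Leakage to controls does not affect the caregiver outcomes, the immediate post-test or the within-arm change in the intervention group. The conclusion assumes that the repeat test goes to both arms. Section 2.1 does not restrict it to one; if it were restricted, there would be no between-arm comparison at that wave to protect.

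The change is worth making because it costs almost nothing and the Discussion itself treats contamination control as critical.

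**What to change.** In section 2.4, replace the limit on the no-sharing rule with: *until the one-month questionnaire has been collected in both arms*. In the same sentence, state that the rule applies to booklets and teaching materials as well as WeChat content. Use the same wording in the instructions to participants.

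Where the one-month result is described, call it knowledge one month after teaching ended, with the take-home booklets still available.

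The cost is a change of wording and one more month of restricted sharing for intervention families. No visit, questionnaire or member of staff is added.
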